## Abstract

**Background:**

Most depressed patients are attended at primary care. However, there are significant shortcomings in the diagnosis, management and outcomes of these patients. The aim of this study is to determine whether the implementation of a structured programme for managing depression will provide better health outcomes than usual management.

**Methods/Design:**

*Design*: A cluster-randomized controlled trial involving two groups, one of which is the control group consisting of patients who are treated for depression in the usual way and the other is the intervention group consisting of patients on a structured programme for treating depression.

*Setting*: 20 primary care centres in the province of Tarragona (Spain)

*Sample*: 400 patients over 18 years of age who have experienced an episode of major depression (DSM-IV) and who need to initiate antidepressant treatment

*Intervention*: A multi-component programme with clinical, educational and organisational procedures that includes training for the health care provider and evidence-based clinical guidelines. It also includes primary care nurses working as care-managers who provide educational and emotional support for the patients and who are responsible for active and systematic clinical monitoring. The programme aims to improve the primary care/specialized level interface.

*Measurements*: The patients will be monitored by telephone interviews. The interviewer will not know which group the patient belongs to (blind trial). These interviews will be given at 0, 3, 6 and 12 months.

*Main variables*: Severity of the depressive symptoms, response rate and remission rate.

*Analysis*: Outcomes will be analyzed on an intent-to-treat basis and the unit of analysis will be the individual patient. This analysis will take into account the effect of study design on potential lack of independence between observations within the same cluster.

**Discussion:**

The effectiveness of caring for depression in primary care can be improved by various strategies. The most effective models involve organisational changes and a greater role of nurses. However, these models are almost exclusively from the USA, and this randomized clinical trial will determine if this approach could be effective to improve the outcomes of depression in primary care in the Spanish health care system.

**Trial registration:**

ISRCTN16384353

## Background

Depressive disorders have been estimated to be the leading cause of disability (i.e. non-fatal burden) in the world [1]. Primary health care, which is the health system's first level of care, is the main ambit in which the most common mental disorders in the population are treatedf, including depression, and the majority of patients suffering from depression are attended exclusively at this care level [2]. However, it has been demonstrated that the detection, diagnosis, treatment and monitoring of patients with depression have significant shortcomings with regard to the model that could be referred to as "the best practice" [3].

In a recent study we found that 14.3% of consecutive primary care patients can be diagnosed with major depression according to DSM-IV criteria [4]. More than half of the depressed patients presented only somatic symptoms and were more difficult to detect by their primary care doctors than patients who openly revealed the psychological nature of their depression [5]. Furthermore, the fact that depression was detected was no guarantee that the patients would receive the appropriate treatment: although 72% of people suffering from depression were detected by their primary care doctor, only 34% received specific treatment with antidepressants while 48% were treated with anxiolytic or hypnotic drugs [6]. In primary care, the rates of non-compliance or early discontinuation of antidepressant prescriptions are high [7] and the evolution of the depressed patient once the treatment has been established is often inadequately monitored, if at all. Therefore, the opportunity to monitor therapeutic compliance and clinical evolution, and to implement measures to improve adherence to the treatment or to adjust inefficient treatments is lost. What is more, access to psychotherapeutic treatment of proven effectiveness as a first line therapy in certain types of mild or moderate depression within the ambit of primary care in the Spanish health system is almost non-existent. Each of these factors compromises the health outcomes that could be obtained in a depressed patient, according to scientific evidence.

In its mental health strategy, the World Health Organisation rightly considers that in order to reduce the impact of depression, in public health terms, the distance that exists between the availability of potentially effective therapeutic measures and the high proportion of depressed patients who are unable to benefit from such options must be overcome. A specific aim in this regard is to provide effective coverage for depression in primary care [8].

In order to improve the diagnosis and treatment of depression in primary care and obtain high rates of efficiency that are closer to the potential effectiveness of available treatments [9], certain strategies of an educational and organisational nature have been proposed, including the training of healthcare professionals, the availability of clinical practice guidelines and strategies to implement them, case management-allocating a central role to non-medical professionals, often nurses-, and collaboration between the primary care level and specialised psychiatric level. The complex models that involve organisational changes and a greater role for nurses rather than the implementation of simple measures (i. e. medical education or access to clinical guidelines as the only measures) have been shown to be most effective [10-12]. The principal limitation of the existing research is that the studies are almost exclusively from the United States, and this raises the question of whether strategies that are effective within one social context and health organisation can be equally effective in other countries with different healthcare structures.

## Methods/Design

### Objectives

The general aim is to determine whether a programme for treating depression leads to better health outcomes than the usual depression management provided in primary care in the Spanish healthcare system. The specific aims are to determine whether the programme for treating depression, compared to usual practice, will reduce the severity of depression, and increase the response and remission rates, and the degree of health-related quality of life at 3, 6 and 12 months.

### Design

This is a controlled trial with a random allocation of clusters (primary healthcare centres) in two alternative branches (see Figure 1):

**Figure 1 F1:**
[figure not shown]
Flowchart: randomisation of centres, and sampling and monitoring of patients.

1. Usual management of depression (control group) and

2. Implementation of a programme to manage depression (intervention group).

The evaluation of the treatment outcomes will be done at patient level, evaluated individually [13].

### Setting and study sample

All of the 20 primary healthcare centres in the Tarragona-Reus Primary Care Area (Catalan Health Institute) in the province of Tarragona, Catalonia, Spain, have agreed to participate. The doctors from each centre who participated in the study had to be full-time employees, remain in the same location for the duration of the study and have a quota of patients assigned.

The doctors participating in the study will ask all patients who have suffered from an episode of major depression (DSM-IV) and who have been advised to take a new course of antidepressants to take part, until they reach their assigned quota of patients.

Patients considered for **inclusion **are those assigned to the doctor, aged ≥18 years, able to be contacted by telephone, who have been diagnosed with an episode of major depression (DSM-IV), have a score of >14 on the PHQ-9 (moderate-severe depression) or a score of 10 to 14 (mild depression) that has persisted for more than one month, and who have not received antidepressant medication in the previous three months.

The following patients will be **excluded**: those who suffer from physical, psychiatric or linguistic limitations or a concurrent illness that impede comprehension/participation in the study evaluations, patients with psychotic or bipolar disorders, patients with alcohol or drug dependence and patients who are pregnant or breastfeeding.

### Allocation of study groups

In order to ensure comparability between the intervention group and the control group, each centre will be paired with another centre with similar features [13]: urban/rural location, the number of participating doctors and the availability of a psychiatrist in the own centre. One of each pair of centres will be randomly allocated as a treatment or a control centre. The pairing and the allocation will be carried out by an independent person not involved in the study.

The centres agree to participate before the random allocation. The patients agree to participate without knowing to which study group their centre has been allocated.

### Intervention

The intervention consists of a multi-component programme that deals with depression based on published scientific evidence. It includes measures that can be reasonably applied within the Spanish health organisation. Such actions are of a clinical, training-based, organisational and health-related educational nature.

The programme includes tools for the systematic and structured evaluation and treatment of depression in primary care. There is an initial 8-hour course based on the clinical guidelines for treating depression recommended by the National Institute for Health and Clinical Excellence (NICE) [14] and designed to improve doctors' knowledge and skills in diagnosing depression, evaluating suicidal risk, clinical treatment, monitoring depression, and modifying the therapy in order to achieve remission in accordance with a treatment algorithm. The training puts the emphasis on the care procedure, active clinical monitoring of depressed patients and the options available when the proposed aims are not achieved (short-term remission and no relapse in the long term). The educational plan includes periodic updates.

A Depression Management Toolkit that contains a treatment algorithm for optimizing the prescription of antidepressant medication is available for the participating doctors.

The programme creates the role of case managers. The case managers are nurses on the staff of the participating primary care centres with specific training (a 8-hour initial course plus periodic updates) in the clinical aspects of depression, antidepressant treatment, secondary effects, treatment adherence and the methods to ensure this, warning signs in the evolution of depression, etc. The case-manager identifies individual, family, and community factors relevant to planning individualized care for depressed patients and their families, provides health education and support on health care needs and resources that help patients to recover or maintain their health and independence. The programme establishes the minimum number of nurse's visits with the patient: in the acute stage, initially one week after inclusion and then monthly until remission; in the continuation and maintenance stage the contacts will be every two/three months. However, the plan of follow-up visits is individualized depending on the nature of the patient and the evolution of the depression. The visits are structured and the patient is provided with information and education on the illness and the treatment, including "self-help" activities and health advice for the patients and their family members. Patients are provided with specifically designed printed and videographic material. Adherence to the therapeutic plan is systematically evaluated, the difficulties are identified so that compliance can be ensured, the possible adverse effects of the treatment are identified and the clinical evolution of the patient is evaluated through systematic use of the Patient Health Questionnaire Depression module (PHQ-9) [15]. All the information, including the score on the PHQ-9, is recorded and sent to the responsible doctors so that they have all the details on the condition and evolution of the patient and can use them to take decisions on the treatment (i. e. the need for changes to the treatment, treating side effects, re-evaluation, consultation with the psychiatrist, etc.).

To improve the primary care/specialised care interface, primary care doctors and psychiatrists are able to consult with each other by telephone or e-mail. Clear criteria for referrals to the specialised level will be established in order to improve the quality of referrals. In any case, whenever patient care is shared between primary and specialised professionals, responsibility for the treatment and monitoring of the patient will be clearly established to prevent any gaps in the care provided. The psychiatrists are given specific directives emphasising the care process and the therapeutic options for depressions that are resistant to treatment for the purpose of achieving short-term remission and preventing long-term relapse.

### Control group (usual management)

The doctors in the centres that continue with standard treatment use their own criteria to attend depressed patients and are allowed to use any resources they consider appropriate, including referral to the specialised level. Although the activities involving the detection and diagnosis of the depression are not included in the evaluation, the doctors in the intervention group could become more aware through the diagnosis of the depression and detect cases with a milder depression, introducing an element of bias in the inclusion of patients. In order to prevent this, the doctors in the control group are given a training session on diagnosing and detecting depression, with the same content as that of the doctors in the intervention group.

### Measurements

The results will be monitored and most of the data collected by means of standard questionnaires conducted by telephone interview by an independent qualified interviewer (a psychologist), who has been trained in telephone interview techniques and in psychiatric nosology. The interviewer will be unaware of which study group the patients being interviewed belong to ("blind"). The follow-up interviews shall take place at 0 (baseline), 3, 6 and 12 months after the inclusion of the patient.

#### Variables and instruments of measurement (See Table 1)

**Table 1 T1:** Study variables

**Instrument**	**Assessment area**	**Applied by**	**Time(s) of assessments**
Sampling form	Age, sex, inclusion/exclusion criteria	Primary care physicians	Baseline
Sociodemographic data form	Age, sex, marital status, educational level, labour status, social class	Research interviewer by means of telephonic interview	Baseline
Duke Severity of Illness Checklist (DUSOI)	Global severity of physical comorbidity	Primary care physicians	Baseline
PRIME-MD; dysthymia and anxiety modules	Common psychiatric comorbidity	Primary care physicians	Baseline
Patient Health Questionnaire (PHQ-9)	Severity of depressive symptoms, remission and response rates	Research interviewer by means of telephone interview	Baseline, 3, 6 and 12 months
Questionnaire	Length of evolution of current depressive episode and previous history of depression.	Research interviewer by means of telephone interview	Baseline
SF-12 Health Survey	Health-related quality of life: mental health and physical health scores	Research interviewer by means of telephone interview	Baseline, 3, 6 and 12 months
Morisky-Green Test	Treatment adherence	Research interviewer by means of telephone interview	Baseline, 3, 6 and 12 months
Use of health resources questionnaire	Number of primary care, psychiatric and emergency visits, and hospitalisations owing to mental health problems	Research interviewer by means of telephone interview	3, 6 and 12 months
Satisfaction with the care received	Satisfaction of the patient with the clinical care got for his depression	Research interviewer by means of telephone interview	3, 6 and 12 months
Exploration of the computer database of pharmaceutical prescription and invoicing	Treatment with antidepressants. Medical prescription and consumption by the patient.	Research assistant	3, 6 and 12 months

##### Main outcome variables

In accordance with the aims of this study, the major outcome variables are response and remission rates and the measurement of depression severity as a continuous variable.

The severity of depressive symptoms will be measured by means of the PHQ-9 [15]. This scale is a brief self-reported diagnosis and a measure of the severity of major depression (DSM-IV). Several studies support its validity, feasibility, and its capacity to detect changes in depressive symptoms over time. A validated Spanish version is available [16]. Published data shows that telephone administration of the PHQ-9 is a reliable procedure for assessing depression [17].

Clinical remission should be the goal of acute treatment for depression [18]. It is defined as virtually complete relief of symptoms and return to full functioning, and is thought of as the optimal goal for the initial phase of treatment of depression [19]. We have adopted a PHQ-9 score of less than 5 as an operational indicator of remission [20].

Response is a defined as a 50% reduction in the severity of the symptoms measured with the PHQ-9 at baseline [15,19].

To measure health-related quality of life, we will use the SF-12 Health Questionnaire [21,22] which will provide two scores: one for physical health and one for mental health.

##### Secondary variables and effect modifiers

At baseline:

- The following sociodemographic data will be collected: sex, age, marital status (single, married/coupled, divorced/separated or widowed), education (no studies, primary, lower secondary, upper secondary and university), labour status, and social class (I, II, IIIN, IIIM, IV and V of the British Registrar General's Scale) [23].

- The severity of the physical comorbidity will be measured using the Duke Severity of Illness Checklist (DUSOI) [24,25]. This checklist will be filled in by each patient's family physician. For each diagnosis of a physical nature, a score is assigned to the symptoms, complications, prognosis and expected response to treatment. The overall severity of the patient, evaluated from 0 to 100, is obtained from an equation that gives a greater coefficient to the main diagnosis and successively lower coefficients to the other diagnoses.

- To assess the most common psychiatric comorbidity in depressed patients we will use the dysthymia and anxiety sections of the Primary Care Evaluation of Mental Disorders (PRIME-MD). This is a 2-stage rapid screening and interview procedure that can generate a range of diagnoses of mental disorders according to DSM-IV criteria [26,27].

- We will establish how long the current depressive episode has been evolving and the previous history of depression.

In the follow-up interviews, besides measuring depressive symptomatology with the PHQ-9 and health-related quality of life with the SF-12 Health Questionnaire:

- Therapeutic compliance will be evaluated by the Morisky-Green Test [28], the self-report compliance (Haynes-Sackett test) [29], and searching the computer databases for pharmaceutical prescription and invoicing.

- The use of health resources in the evaluated period is determined by means of interviewing the patient: number and type of primary care, psychiatric and emergency visits and hospitalisations for mental health problems.

- The patients' satisfaction with the care received is evaluated using a single item (a Likert scale with five response options) [30].

### Statistical methods

#### Sample size

To calculate the sample size, we consider the remission rate at six months as the main result variable.

On the basis of published research data [31], we assume that this will be 30% in the control group and we aim to detect a difference of 16% or more between this group and the intervention group.

Accepting an alpha risk of 0.05 and a beta risk of <0.20 in a bilateral contrast and assuming a 15% loss in continuing the treatment, we would need 169 subjects in each group in a simple random sampling.

To correct this figure for design effect (cluster randomisation) [13,32] we shall use the formula:

Deff = 1 + (m - 1) × ICC

where Deff: design effect, m: size of clusters and ICC: intraclass coefficient correlation.

Provisionally assuming an ICC = 0.01 and m = 20, the Deff will be 1.19. Thus, each group needs to consist of 201 subjects (1.19 × 169 = 201) divided into 10 clusters of 20 patients.

We have no reliable data on the ICC in the sample and in the variables we studied and we have provisionally used a prudent figure that will be checked once the data is available.

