#### Analysis strategy

Randomisation is performed at primary care centre level and the results of the treatment will be analysed at individual patient level [13]. The analyses shall be per intent to treat.

First we will compare the intervention group with the control group in order to verify that there are no significant differences between the two groups (socio-demographic data, clinical baseline data, etc.). We shall use the mean (Standard Deviation) in the continuous variables and percentages in the categorical variables. For comparisons we shall use the Student-T test for continuous variables and the Chi-squared test for categorical variables. Non-parametric tests may also be used.

The main variables of the result are the depressive symptomatology (PHQ-9 score), response to treatment (reduction of 50% or more in the baseline score), remission (score of <5) and quality of life related to health (SF-12 score) at 3, 6 and 12 months.

Process variables include the number of visits for depression to the primary care centre, psychiatrist, emergencies and hospitalisations and the continued use of anti-depressants over 3 months.

We shall use the analysis of the linear mixed models of the SPSS v.15 statistical package, including the two effects, fixed and random, to analyse the effect of the continuous result variables (depression symptomatology [PHQ-9 score], quality of life related to health [SF-12 score]). We shall analyse the effect of the treatment on the categorical result variables (response and remission rates) by analysing the general linear models of the SPSS v.15. The random effects of these linear models (mixed and general) provide the structure that enables us to take into account the effect of randomisation by clusters owing to a potential lack of independence between observations within the same centre [33].

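### The sample size is built on one main outcome, remission at six months, but the outcome and analysis sections name several unranked main outcomes, so the stated 5% error rate and 80% power do not clearly belong to the trial's conclusion

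*Protocol article*

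**What the plan says.** The protocol article describes its main outcome in three ways.

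- **Sample size:** one outcome at one time. "To calculate the sample size, we consider the remission rate at six months as the main result variable". The design values attach to it: "we assume that this will be 30% in the control group and we aim to detect a difference of 16% or more", and "Accepting an alpha risk of 0.05 and a beta risk of <0.20 in a bilateral contrast".
- **Main outcome variables (opening sentence), and the abstract:** three outcomes, with no time point. In the former, "the major outcome variables are response and remission rates and the measurement of depression severity as a continuous variable". The same section then goes on to describe SF-12, with separate physical and mental scores, under the same heading.
- **Analysis strategy:** four named variables at three times. The list opens "The main variables of the result are the depressive symptomatology (PHQ-9 score), response to treatment", continues with remission, and ends with "quality of life related to health (SF-12 score) at 3, 6 and 12 months".

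The Objectives section lists severity, response, remission and quality of life at all three times, also unranked. Secondary variables and process variables are set apart elsewhere. Nothing ranks the main variables among themselves, and the Analysis strategy does not single out six-month remission.

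**The concern.** The alpha and power in a sample size calculation describe a trial's conclusion only if that conclusion rests on the comparison used in the calculation. Here the section that governs the analysis gives equal standing to outcomes and time points for which the trial was not sized.

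Suppose PHQ-9 score differs at 3 months but remission does not differ at six. The document does not say whether the programme has been shown to work, and the choice could be made after the data are seen. The answer has a practical consequence: the Ethical aspects section guarantees access to the programme in all participating centres if it proves effective.

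**Working it through.** **1. The plan's own figure.** Inputs from Sample size: 30% control, 46% intervention (the 16% read as an absolute difference), two-sided 0.05, power 80%, 15% loss.

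Pooled two-proportion formula, with mean proportion 0.38:

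n = [1.960 × √(2 × 0.38 × 0.62) + 0.8416 × √(0.30 × 0.70 + 0.46 × 0.54)]² / 0.16²
= (1.3454 + 0.5698)² / 0.0256 = 143.3

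143.3 / 0.85 = 168.6, which rounds up to 169. (Rounding to 144 before the loss correction gives 170.) This matches "assuming a 15% loss in continuing the treatment, we would need 169 subjects in each group in a simple random sampling".

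Design effect: "Provisionally assuming an ICC = 0.01 and m = 20, the Deff will be 1.19". Check: 1 + 19 × 0.01 = 1.19, and 1.19 × 169 = 201.1. The sample size is reproduced for a single primary outcome.

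**2. How many comparisons the text allows.**

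- Three PHQ-9 outcomes (score, response, remission) × 3 times = 9
- The four variables of Analysis strategy, SF-12 counted once, × 3 times = 12
- The same with SF-12 as two scores × 3 times = 15

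**3. Chance of at least one false positive, if each is tested at two-sided 0.05.** Under independence this is 1 − 0.95^k in either direction and 1 − 0.975^k in favour of the programme. The correlated figures come from simulating k normal test statistics with a common correlation ρ (400,000 draws). The values of ρ are assumed; the documents give none.

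| Comparisons | Direction counted | Independent | ρ = 0.5 | ρ = 0.8 |
|---|---|---|---|---|
| 9 | either | 37.0% | 26.9% | 16.5% |
| 9 | favourable | 20.4% | 13.5% | 8.3% |
| 12 | either | 46.0% | 31.9% | 18.6% |
| 12 | favourable | 26.2% | 15.9% | 9.3% |
| 15 | either | 53.7% | 36.2% | 20.4% |
| 15 | favourable | 31.6% | 18.2% | 10.2% |

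The benchmark for a single test is 5% in either direction and 2.5% in favour of the programme.

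**4. What equal standing would cost in power.** With 10 clusters of 20 per group, the effective number is 200 × 0.85 / 1.19 = 142.9 per group. Power for six-month remission is 80% at alpha 0.05. With a Bonferroni split it falls to 51% for 9 comparisons (alpha 0.05/9 = 0.0056) and 44% for 15 (alpha 0.05/15 = 0.0033). Restoring 80% with 15 comparisons would need 261 per group, 308 after 15% loss, and 308 × 1.19 = 366.5, so 367 after the design effect. The planned 201 therefore fits one primary outcome and not a set of equals.

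**The case against.** Several points on the other side are sound.

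- **The sample size is coherent.** It names one outcome and its arithmetic holds. The text to correct is in Analysis strategy, Main outcome variables and the abstract. This stands.
- **The lists are nested.** Remission appears in all of them, and SF-12 is described under the main-outcome heading, so Main outcome variables and Analysis strategy nearly agree. This stands, but nesting does not say which member of the list decides the trial.
- **A reader might infer that the plan runs 15 tests at 0.05, any one of which makes the trial positive, with a 54% chance of a false claim.** The documents do not support that. Fifteen is the top of a range of 9 to 15. The only alpha is attached to the sample size contrast. No section says that any single significant result is enough. A mixed model for the continuous outcomes could use fewer tests than one per visit. The 54% also needs independence, which cannot hold when three outcomes come from the same PHQ-9 and all are repeated over time, and it counts errors against the programme as well as for it.
- **A testing order and a multiplicity adjustment are commonly left to the SAP, which is not shown.** Their absence here is not a fault. The inconsistency is different: the article states its main outcome and does so in conflicting ways, and an SAP would have to choose among them.

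**Conclusion.** The point holds as an inconsistency in naming the primary outcome. The 5% error rate and 80% power belong to remission at six months, while the sections that define and analyse the outcomes give equal rank to 9 to 15 comparisons.

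If each were tested at 0.05, with an assumed common correlation of 0.5 to 0.8, the chance of at least one false positive is about 16% to 36% in either direction, or about 8% to 18% favouring the programme. The 37% to 54% under independence is an upper reference only. These figures rest on two things the documents do not state: the per-comparison alpha and the correlation. The inconsistency itself rests on neither.

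**What to change.** In the abstract, Main outcome variables and Analysis strategy, name remission (PHQ-9 below 5) at six months as the single primary outcome, tested at two-sided 0.05, to match Sample size. Label PHQ-9 score, response, both SF-12 scores and all 3- and 12-month assessments secondary, and say that they cannot by themselves carry the claim of effectiveness. A fixed testing order for the secondary outcomes is optional and can be left to the SAP.

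The cost is wording: the 201 per group, the interviews and the instruments are unchanged. The downside is that a result on another outcome or time point can no longer be called the main finding. The change should be made before outcomes are compared by group.

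### The stated beta risk below 0.20 makes no allowance for having only 20 centres: with the planned 15% loss, power on 18 degrees of freedom is about 75–77%

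*Protocol article*

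**What the plan says.** All the relevant statements are in the protocol article, mostly under Sample size.

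- Endpoint: "we consider the remission rate at six months as the main result variable".
- Effect: "we assume that this will be 30% in the control group and we aim to detect a difference of 16% or more".
- Error rates: "Accepting an alpha risk of 0.05 and a beta risk of <0.20 in a bilateral contrast".
- Loss: "assuming a 15% loss in continuing the treatment, we would need 169 subjects in each group in a simple random sampling".
- Clustering: "Provisionally assuming an ICC = 0.01 and m = 20, the Deff will be 1.19", so that "each group needs to consist of 201 subjects (1.19 × 169 = 201) divided into 10 clusters of 20 patients".
- Basis of the ICC: the section says there are no reliable data on it for this sample and these variables, and adds that "we have provisionally used a prudent figure that will be checked once the data is available".

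Three other sections bear on the point. Setting and study sample says that all 20 centres of the area take part. Allocation of study groups forms matched pairs of centres and randomises within each pair. Analysis strategy analyses individual patients by intention to treat, with random effects to allow for dependence within a centre. It names no term for the pair and states no rule for degrees of freedom.

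**The concern.** The two-proportion formula and the design effect both work with normal quantiles, as if the variance between centres were known. In this trial it has to be estimated from 20 centres. A test that reflects this uses a t reference distribution with few degrees of freedom, which raises the critical value and lowers power. The plan has no reserve to absorb that loss, because the enrolled number is set almost exactly at what the normal formula requires.

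The ICC wording adds to this. In Deff = 1 + (m − 1) × ICC, a cautious choice is a value unlikely to be exceeded. A text that reports no reliable data cannot say that of 0.01. No consequence is attached to the later check of the ICC.

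At stake is how a null result is read. If the programme shows no significant benefit, readers will take it as coming from a trial with at least 80% power for a 16-point difference.

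**Working it through.** **Inputs.** From Sample size: rates 0.30 and 0.46, two-sided alpha 0.05, power 0.80, loss 15%, ICC 0.01, m = 20, 10 centres of 20 per arm. Derived here, not stated: 20 − 2 = 18 between-centre degrees of freedom, with pairing ignored, as in the model that Analysis strategy describes.

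**1. Reproduce the plan.**

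n per arm = [1.96·√(2·0.38·0.62) + 0.8416·√(0.30·0.70 + 0.46·0.54)]² / 0.16² = 143.3

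143.3 / 0.85 = 168.6, so 169. Deff = 1 + 19 × 0.01 = 1.19. 1.19 × 169 = 201.1, so 201. All three figures agree with the plan.

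**2. Slack.** Enrolled: 10 × 20 = 200 per arm. Analysed: 200 × 0.85 = 170, or 17 per centre. The design effect is 1.19 at m = 20, or 1 + 16 × 0.01 = 1.16 at the 17 who remain. Effective n per arm is 170/1.19 = 142.9 or 170/1.16 = 146.6, against 143.3 needed. Power on the plan's normal formula is 79.9% or 80.9%.

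**3. Allow for 18 degrees of freedom.** The critical value rises from 1.960 to 2.101. The unpooled SE is √(0.4584 / effective n) and the pooled SE is √(0.4712 / effective n). The noncentrality is 0.16 / SE, and power comes from the noncentral t distribution.

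| Deff | SE used | SE | Noncentrality | Power, 18 df |
|---|---|---|---|---|
| 1.19 | unpooled | 0.0566 | 2.82 | 76.2% |
| 1.19 | pooled | 0.0574 | 2.79 | 75.0% |
| 1.16 | unpooled | 0.0559 | 2.86 | 77.2% |
| 1.16 | pooled | 0.0567 | 2.82 | 76.1% |

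Beta is therefore about 0.23–0.25. A beta-binomial simulation (40,000 trials, 10 centres per arm, 17 patients per centre, t-test on centre proportions) gave 76.5%.

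**4. Detectable difference.** 80% power on 18 df needs a noncentrality of about 2.96. With the unpooled SE:

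- Deff 1.16: √((0.21 + 0.466·0.534)/146.6) = 0.0560, and 2.96 × 0.0560 = 0.166
- Deff 1.19: √((0.21 + 0.468·0.532)/142.9) = 0.0567, and 2.96 × 0.0567 = 0.168

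That is 16.6–16.8 points. The pooled SE at Deff 1.16 also gives 16.8.

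**5. If nobody is lost from the analysis.** Effective n = 200/1.19 = 168.1, SE 0.0522 (unpooled), noncentrality 3.06. Power on 18 df is 82.6% (81.5% with the pooled SE), so the target is met.

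**6. Sensitivity to the ICC.** Values above 0.01 are assumptions made here to show the range. With 17 analysed per centre:

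| ICC | Deff | Power, normal formula | Power, 18 df |
|---|---|---|---|
| 0.01 | 1.16 | 81% | 76–77% |
| 0.02 | 1.32 | 76% | 71–72% |
| 0.03 | 1.48 | 71% | 66–67% |
| 0.05 | 1.80 | 62% | 57–58% |

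On 18 df, 80% is reached only if the ICC is about 0.003–0.005 or less. On the normal formula it is lost once the ICC exceeds about 0.012.

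**The case against.** The strongest reply is that nothing is miscalculated. The standard formula with a design effect was applied correctly, and a correction for few clusters is a refinement. The degrees of freedom are inferred: the article analyses individual patients and gives no such rule, which is a detail that an analysis plan may supply. A mixed model that estimates the centre variance as zero could use more than 18. The shortfall is only 3–5 points of power, or 0.6–0.8 points of difference, within the uncertainty of the 30% planning rate. It also depends on what the 15% means. The text describes it as stopping treatment, and under intention to treat those patients could still be analysed.

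Much of this stands. It limits the size and certainty of the point, and it rules out calling 169, 1.19 or 201 an error. It does not remove the point. The plan inflates the sample for the 15%, which makes sense only if those patients are expected to be missing from the analysis. It also randomises 20 centres and commits to random effects for centre, so 18 is the natural benchmark.

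A reader might infer more than the documents support:

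- **That power is as low as 70–72%.** This follows if the matched pairs are kept in the analysis (10 − 1 = 9 df). Analysis strategy names no pair term, so the figure does not describe the planned test.
- **That the true ICC is higher and power is far below 80%.** Nothing in the documents shows that 0.01 is too low. They call it provisional and say openly that reliable data are lacking.
- **That the later check of the ICC is offered as a way to restore power.** The text does not say so.

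**Conclusion.** The point holds in a limited form. The arithmetic is right, but the power attached to it is not delivered once the test reflects 20 randomised centres. At the plan's own ICC, power for 30% against 46% is about 75–77%, and 80% power belongs to a difference of about 16.6–16.8 points.

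This rests on two assumptions: that inference uses about 18 degrees of freedom, and that the 15% are lost from the analysis. If they are analysed, power is about 82–83% and the stated target stands.

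Separately, describing the ICC as prudent is unsupported by the section's own account of its data, although the value is openly provisional. The shortfall is modest and does not call for more centres or patients.

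**What to change.** In Sample size:

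1. Restate the power, for example: *With 20 centres, 400 patients, 15% lost to analysis and an ICC of 0.01, power for 30% against 46% is about 75–77% (t test, 18 degrees of freedom).* Alternatively, keep 80% power and give the detectable difference as about 16.6–16.8 points.
2. Say whether the 15% are lost from the analysis or only stop treatment, since the conclusion turns on it.
3. Delete the word prudent, and call 0.01 a working assumption without supporting data.
4. Show power over an assumed ICC range. On 18 df with 17 analysed per centre it is about 71–72% at 0.02 and 57–58% at 0.05.

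Adjustment for baseline PHQ-9 should not be offered as making up the shortfall, because the documents give no figure from which a gain could be worked out.

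The change is to wording only. Its cost is a slightly less favourable stated power.
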